In exploratory analyses, we hypothesize that greater tDCS exposure will be associated with larger reductions in depressive symptom severity and that participants demonstrating greater improvement in depressive symptoms may also exhibit lower opioid requirements and modest improvements in spine-related patient-reported outcomes. These analyses are intended to be hypothesis-generating and to inform outcome selection and effect size estimation for future controlled trials evaluating preoperative neuromodulation interventions in spine surgery populations.

This study is not powered to establish efficacy for clinical or surgical outcomes. Rather, it is designed to generate feasibility, acceptability, and preliminary signal data to guide the design of subsequent randomized studies.

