### Eligibility criteria

Inclusion criteria:

1 Adults aged 22–75 years old2 Clinical diagnosis of unipolar major depressive disorder as determined by the patient’s established managing clinician3 At least moderate depressive symptom severity, defined as a baseline self-reported Montgomery–Åsberg Depression Rating Scale (MADRS-S) score ≥204 Being evaluated or scheduled for elective, non-revision lumbar spine surgery (prior spine surgery is not a contraindication)5 Either:

not receiving antidepressant medication, orreceiving antidepressant medication and/or psychotherapy at a stable dose or frequency for ≥6 weeks before enrollment, with agreement to maintain treatment stability during the study

6 Ability to use the Flow device independently at home and to complete remote assessments, including use of a smartphone or tablet to guide sessions and transmit adherence data7 Under the care of a primary care physician or mental health provider8 Capacity to provide informed consent

Exclusion criteria: Exclusion criteria are designed to ensure participant safety, minimize risks associated with electrical stimulation, and improve interpretability of study outcomes. Key exclusions include:

Neurologic and device-related exclusions

History of seizure disorder, epilepsy, loss of consciousness related to seizures, or other neurologic conditions that may increase riskPresence of implanted electronic or metallic devices (cranial or otherwise) that may pose safety concerns (e.g., pacemakers or implanted neurostimulators)Neurocranial defects

Psychiatric exclusions

Clinically unstable psychiatric conditions requiring urgent treatment (e.g., acute suicidality, psychosis, or mania)Current or past bipolar disorder, psychotic disorder, or obsessive-compulsive disorder

tDCS-specific and medication exclusions

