### Recruitment, screening, and informed consent

Potential participants will be identified by reviewing spine surgery clinic schedules. Eligible participants will complete written informed consent before any study-specific procedures. The consent process will emphasize voluntariness, the ability to withdraw at any time, and that participation will not affect standard surgical care. Surgical complexity will be quantified using validated procedure-based metrics derived from the operative record (e.g., surgical invasiveness/complexity indices and number of operative levels).

At enrollment, participants’ antidepressant treatment history will be systematically documented, including current and prior antidepressant medication trials (agent, dose, duration, and response), prior psychotherapy, and the number of failed adequate antidepressant trials in the current depressive episode. Treatment resistance status will not be used as an inclusion or exclusion criterion but will be reported descriptively to characterize the sample and support comparison with prior home-based tDCS studies that have enrolled treatment-resistant cohorts.

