### Concomitant care

All participants will continue to receive standard surgical and perioperative care without modification. Concurrent treatment for depression, including pharmacotherapy and/or psychotherapy, will be permitted. Changes in depression-related treatment during the intervention and follow-up period—including medication initiation, discontinuation, or dose adjustment, as well as psychotherapy initiation—will be recorded systematically to support contextualization of outcome trajectories and exploratory sensitivity analyses.

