#### Exploratory clinical outcomes: depressive symptoms

Clinical outcomes are exploratory (Table 1). The principal exploratory clinical outcome is change in depressive symptom severity measured using MADRS-S. Depressive symptoms will be assessed at baseline (week 0) before initiation of tDCS, at week 1, at the end of the initiation phase (week 4), at week 7, and at a preoperative assessment conducted within a defined window before surgery (week 8–10+). Observed changes in depressive symptom severity will be interpreted in the context of the study’s feasibility-focused design. These analyses are not intended to establish efficacy, but rather to generate preliminary signal and variability estimates to inform future trial design.

**Table 1 tab1:** Exploratory outcomes.

Domain	Measure	Baseline	Timepoints*	Pre-op**	Post-op
Depression	MADRS-S	X	X	X	—
Spine disability	Oswestry disability index (ODI)	X	—	X	X (6 wks or 3 mos)
Pain intensity	Back pain NRS (0–10)	X	X	X	X
	Leg pain NRS (0–10)	X	X	X	X
Pain-related function	PROMIS pain interference (SF)	X	Optional	X	X
Physical function	PROMIS physical function (SF)	X	—	X	X
Opioid exposure	Baseline outpatient opioid use (MME)	X	—	—	—
Opioid utilization	Inpatient postoperative MME	—	—	—	X
	30-day outpatient postoperative MME	—	—	—	X

*Week(s) 0, 1, 4, 7, 10, and preoperatively (as applicable). **≤7 days before surgery.

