#### Exploratory clinical analyses: depressive symptoms

Exploratory analyses will evaluate changes in depressive symptom severity over time. The principal exploratory clinical outcome is the change in MADRS-S score from baseline to the preoperative assessment. Change from baseline to the end of the initiation phase (week 4) will be examined as an early signal of response following intensive treatment initiation.

Longitudinal changes in depressive symptoms will be examined using mixed-effects models to account for repeated measures and variable treatment exposure. Models will include fixed effects for time and baseline symptom severity, with random effects to account for within-participant correlation. These analyses are exploratory and not powered to establish efficacy. Exploratory response and remission rates based on standard MADRS-S thresholds will be summarized descriptively at the preoperative time point.

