## Discussion

This prospective pilot study is designed to evaluate the feasibility and acceptability of delivering home-based transcranial direct current stimulation (tDCS) as a preoperative intervention elective lumbar spine surgery candidates with MDD. The primary contribution of this work is implementation-focused: to determine whether a remotely delivered neuromodulation intervention can be initiated and sustained within the variable and time-constrained preoperative surgical workflow. By using a dose-to-time framework with pre-specified exposure tiers, this study addresses a practical challenge unique to elective surgery—heterogeneity in time from enrollment to operation—and provides a pragmatic model for preoperative mental health optimization.

Beyond feasibility, this study aims to generate preliminary estimates of depressive symptom change and variability using a validated self-report instrument (MADRS-S). These exploratory clinical data are not designed to establish efficacy, but rather to inform endpoint selection, assessment timing, and sample size assumptions for future trials. In addition, exploratory evaluation of perioperative recovery–relevant outcomes, including pain, disability, and opioid utilization, provides an initial signal as to whether preoperative mood modulation may be meaningfully related to downstream recovery trajectories.

Several anticipated challenges are inherent to this study design. Adherence may vary over longer preoperative intervals, and treatment exposure will be constrained by surgical scheduling. Concomitant changes in depression treatment during the preoperative period may introduce additional variability. Surgical heterogeneity and baseline differences in pain and disability further complicate the interpretation of exploratory recovery outcomes. These challenges are intentionally addressed through feasibility-first endpoints, as-treated analyses, tiered exposure definitions, and descriptive modeling approaches, which prioritize transparency and interpretability over causal inference.

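### As worded, criterion 5's first branch admits every psychotherapy-only patient, so its ≥6-week stability rule never binds for patients on psychotherapy alone (minor; exploratory MADRS-S results only)

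*Protocol article*

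**What the plan says.** The Eligibility criteria section of the protocol article sets criterion 5 as two alternatives, and meeting either is enough. The first is that the patient is "not receiving antidepressant medication". It mentions neither psychotherapy, nor a stability period, nor any undertaking about later treatment. The second covers patients receiving "antidepressant medication and/or psychotherapy at a stable dose or frequency for ≥6 weeks before enrollment, with agreement to maintain treatment stability during the study". Its and/or takes in three groups: medication only, psychotherapy only, and both.

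Three other places bear on the point:

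- Recruitment, screening, and informed consent: at enrollment, "antidepressant treatment history will be systematically documented, including current and prior antidepressant medication trials (agent, dose, duration, and response), prior psychotherapy" are covered. This is a record and not a condition of entry.
- Concomitant care: concurrent psychotherapy is allowed. "Changes in depression-related treatment during the intervention and follow-up period" are recorded, including the start of psychotherapy, for context and for exploratory sensitivity analyses.
- Exploratory clinical analyses: depressive symptoms: the principal exploratory outcome is MADRS-S change from baseline to the preoperative assessment. In addition, "Exploratory response and remission rates based on standard MADRS-S thresholds will be summarized descriptively at the preoperative time point".

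The exploratory results have a stated use. The depressive-symptom outcomes are meant "to generate preliminary signal and variability estimates to inform future trial design", and the Objectives and hypotheses section says the exploratory analyses are "to inform outcome selection and effect size estimation for future controlled trials".

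**The concern.** The second branch names psychotherapy and attaches a condition to it. The first branch lets the same patients in without that condition. A psychotherapy-only patient whose therapy began last week is as eligible as one whose therapy has been steady for a year.

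What is at stake is the reading of the MADRS-S results. With no control arm, improvement from newly started psychotherapy cannot be told apart from improvement seen with tDCS. The stability rule is the natural place to limit this, and the Discussion recognises the related problem: "Concomitant changes in depression treatment during the preoperative period may introduce additional variability". That sentence concerns changes after the preoperative period has begun. Therapy begun shortly before enrollment raises the same difficulty but falls outside that period.

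**Working it through.** The plan gives no figure to reproduce. The check is one of logic, followed by simple arithmetic on size.

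**1. Criterion 5 as written.** A patient is eligible if (no medication) OR (medication and/or psychotherapy, each treatment received being stable for ≥6 weeks, AND agreement to stay stable). Listing every combination of stability and agreement:

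| Group | Combinations | Eligible as written | Eligible if first branch read *neither medication nor psychotherapy* |
|---|---|---|---|
| Untreated | 2 | 2 | 2 |
| Psychotherapy only | 4 | 4 | 1 |
| Medication only | 4 | 1 | 1 |
| Both | 8 | 1 | 1 |

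For psychotherapy only, the four combinations are stable or not, crossed with agreeing or not. All four pass through the first branch. The second branch admits one of them (stable and agreeing), which the first has already admitted. So the rule excludes no one in this group. It does bind in the other two groups that the second branch names.

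**2. An exclusive either/or.** If a patient had to meet exactly one branch, the stable and agreeing psychotherapy-only patient would meet both and be barred, while the other three combinations would still enter. That reading is worse.

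**3. Does another rule close the gap?** None of the listed exclusions concerns recent psychotherapy. The enrollment history documents prior psychotherapy, but the article does not make it a condition and does not expressly ask when ongoing therapy began. The Concomitant care record covers the intervention and follow-up period, so a start before enrollment is not clearly a recorded change.

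**4. Overlap with treatment.** Dosing schedule: a minimum planned 4 weeks and a maximum of 10 weeks of tDCS. Assume psychotherapy began 0–6 weeks before enrollment, continued, and tDCS started at enrollment. At the end of tDCS it has run from 0 + 4 = 4 weeks to 6 + 10 = 16 weeks. It overlaps the whole course.

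**5. Size.** Sample size justification: 20 evaluable participants.

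- Weight of one participant in a response or remission rate: 1/20 = 5 percentage points, as a ceiling.
- Largest 95% sampling half-width at n = 20: 1.96 × √(0.5 × 0.5 / 20) = 0.219, about 22 points.
- The number k of such participants is not given. At most, the shift is 5k points: 0 for k = 0, 5 for k = 1, 10 for k = 2.
- For mean MADRS-S change, k participants who each improve by d extra points shift the mean by k × d / 20. The documents give neither k nor d, so no value can be put on it.

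**The case against.** The strongest reply is that the intent is plain. The second branch names psychotherapy, so a sensible screener would apply it to a patient in psychotherapy and treat the first branch as meaning untreated. That is probably what was meant. But the words do not say it, and two screeners could decide differently on the same patient.

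Second, the Concomitant care section does more than permit psychotherapy: it records its initiation and foresees exploratory sensitivity analyses, and treatment history is documented at enrollment. This stands as mitigation for changes during the study. It does not clearly reach therapy begun before enrollment, and it is not an entry check.

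Third, the result affected is exploratory. The study is stated not to be powered for efficacy, and the Discussion already concedes placebo and context effects, regression to the mean and spontaneous fluctuation. Stable psychotherapy, which is allowed, also runs alongside tDCS. All of this stands, and it is why the point is minor: the pre-post change could not be attributed to tDCS even with perfect wording. What remains is one avoidable source of change that the plan's own rule addresses but does not catch.

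A reader might also infer that, because the stability agreement sits only in the second branch, untreated patients should be asked for it too. The gap does not support that. Untreated patients have no regimen to hold steady, and treatment they start later is already recorded.

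**Conclusion.** The point holds, for patients on psychotherapy alone. As written, neither the ≥6-week rule nor the stability agreement can affect their entry, and nothing else in the article screens for recently begun psychotherapy. The consequence is a possible contribution to the uncontrolled exploratory MADRS-S change, response and remission.

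Severity is minor. The effect is probably small: up to 5 percentage points per such participant on a rate whose sampling half-width may reach about 22 points, with the number of such participants unknown and possibly zero. These figures assume 20 evaluable participants; the overlap of 4 to 16 weeks assumes that therapy continues throughout tDCS.

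A reader might infer that the stability rule fails generally, or that the study's main conclusions are compromised. Neither follows. The rule works for everyone on medication, with or without psychotherapy, and the primary feasibility and acceptability conclusions are unaffected. Nor do the documents show that patients with unstable psychotherapy would in practice be enrolled; they show only that the wording would let them in.

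**What to change.** Change only the first branch of criterion 5, so that it reads: *receiving neither antidepressant medication nor psychotherapy*. Leave the second branch as it stands, including the agreement that runs for the whole study. Eligibility of untreated and medicated patients does not change. Psychotherapy-only patients then enter only if stable for ≥6 weeks and willing to stay so. No change to the analysis is needed.

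The cost is a small amendment, since the Ethics and dissemination section reports that IRB approval is in place; one screening question on when psychotherapy began or last changed; and an occasional candidate delayed or missed, out of a planned 24–25. The change is best made before enrollment starts, because entry decisions cannot be revisited afterwards.

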### Recruitment, screening, and informed consent

Potential participants will be identified by reviewing spine surgery clinic schedules. Eligible participants will complete written informed consent before any study-specific procedures. The consent process will emphasize voluntariness, the ability to withdraw at any time, and that participation will not affect standard surgical care. Surgical complexity will be quantified using validated procedure-based metrics derived from the operative record (e.g., surgical invasiveness/complexity indices and number of operative levels).

At enrollment, participants’ antidepressant treatment history will be systematically documented, including current and prior antidepressant medication trials (agent, dose, duration, and response), prior psychotherapy, and the number of failed adequate antidepressant trials in the current depressive episode. Treatment resistance status will not be used as an inclusion or exclusion criterion but will be reported descriptively to characterize the sample and support comparison with prior home-based tDCS studies that have enrolled treatment-resistant cohorts.

### Intervention: home-based tDCS regimen

Participants will receive a home-based tDCS intervention using a wearable headset (Flow FL-100 home tDCS headset (Buy or rent the flow headset—flow neuroscience, 2026) (Figures 1, 2) paired with a smartphone application that guides session delivery and logs adherence. Stimulation will be delivered at 2 mA for 30 min per session using a bilateral dorsolateral prefrontal cortex montage (anode over left DLPFC and cathode over right DLPFC), consistent with commonly used DLPFC-targeted protocols and the device’s pivotal trial (Woodham et al., 2025).

### Dosing schedule

All participants initiate treatment using a standardized dosing cadence derived from prior Flow Neuroscience trials. During the initiation phase (weeks 1–3), participants complete five tDCS sessions per week (15 sessions total). Beginning in week 4, participant’s transition to a maintenance phase of three sessions per week, continuing until the date of surgery or a maximum treatment duration of 10 weeks, whichever occurs first.

Because the interval between enrollment and surgery varies across participants, the total treatment duration is variable as well. The minimum planned exposure is 4 weeks, with a target exposure of 6–10 weeks when feasible. A treatment session is classified as complete if the full 30-min stimulation protocol is delivered, as recorded by the device, in accordance with protocol parameters. Sessions interrupted or terminated before 30 min will be classified as partial (≥20 min of stimulation delivered) or incomplete (<20 min of stimulation delivered). Only sessions classified as complete will count toward exposure tier classification. Partial and incomplete sessions will be documented and reported descriptively, with sensitivity analyses examining whether their inclusion materially affects feasibility metrics.

### Exposure tiers

To accommodate variability in surgical scheduling, participants are categorized based on the number of completed tDCS sessions before surgery:

Tier A (initiation complete): ≥15 sessions (~3–4 weeks)Tier B (initiation + ≥ 1 maintenance week): ≥21 sessions (~5 weeks)Tier C (full exposure): 36 sessions (10-week regimen)

Participants will be analyzed on an as-treated basis, by the exposure tier achieved, regardless of intended treatment duration or if they proceeded with surgery.

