#### Exploratory clinical outcomes: perioperative recovery

Additional exploratory outcomes are included to examine whether preoperative home-based tDCS exposure is associated with changes in pain-related disability, functional status, and analgesic utilization in elective lumbar spine surgery candidates. Exploratory analyses will examine associations between tDCS exposure—both by pre-specified exposure tier and as a continuous measure of completed sessions—and changes in these outcomes.

Spine-specific disability will be assessed using ODI, administered at baseline, during the preoperative assessment window, and at a single exploratory postoperative time point. Pain intensity will be measured using 11-point numeric rating scales (NRS) for both back pain and leg pain. Pain-related functional impact will be assessed using the PROMIS Pain Interference short form, and overall physical function will be assessed using the PROMIS Physical Function short form.

Analgesic utilization will be evaluated using standardized morphine milligram equivalent (MME) calculations. Exploratory opioid outcomes will include baseline outpatient opioid exposure prior to initiation of tDCS, inpatient postoperative opioid utilization from surgery to hospital discharge, and cumulative outpatient opioid utilization during the early postoperative period.

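### Exposure is counted to surgery, but preoperative outcomes are taken up to 7 days earlier or, after week 10, following an untreated gap; exposure-response analyses should count sessions to the assessment date

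*Protocol article*

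**What the plan says.** Four parts of the protocol article bear on this point.

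- **Exposure tiers:** "participants are categorized based on the number of completed tDCS sessions before surgery". The top tier is given as "Tier C (full exposure): 36 sessions (10-week regimen").
- **Dosing schedule:** "During the initiation phase (weeks 1–3), participants complete five tDCS sessions per week (15 sessions total"). From week 4 the planned rate drops to three a week. The end of treatment is described as "continuing until the date of surgery or a maximum treatment duration of 10 weeks, whichever occurs first". On duration: "The minimum planned exposure is 4 weeks, with a target exposure of 6–10 weeks when feasible".
- **Exploratory clinical outcomes: depressive symptoms, Table 1 footnotes:** the preoperative measurement is taken "≤7 days before surgery". Interim timepoints are weeks 0, 1, 4, 7 and 10 as applicable. They apply to MADRS-S and the two pain ratings, are optional for PROMIS Pain Interference, and are not scheduled for ODI or PROMIS Physical Function.
- **Exploratory clinical outcomes: perioperative recovery:** exposure is related to changes in the recovery outcomes "both by pre-specified exposure tier and as a continuous measure of completed sessions". The matching analysis section repeats this. Objectives and hypotheses adds the hypothesis that more exposure goes with a larger fall in depressive symptoms.

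The principal exploratory outcome is the MADRS-S change from baseline to the preoperative assessment. Nothing in the article stops the session count at the assessment date, and nothing sets a maximum time from the last session to the assessment.

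**The concern.** An exposure-response analysis should use the exposure received by the time the outcome was measured. Here the two clocks differ.

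Before week 10, the exposure clock runs to surgery while the outcome may be read up to a week earlier. Some counted sessions then cannot have influenced the outcome, and the tier label can be one step too high.

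After week 10 the mismatch reverses. The count can no longer rise, but the assessment moves later with surgery. Participants with the same count can therefore be measured while on treatment or weeks after stopping. If benefit wanes, this would flatten the upper end of the exposure-response relation.

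The protocol says these analyses are meant to inform outcome selection and effect-size estimates for later trials, so the exposure variable should be properly aligned in time.

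**Working it through.** **Inputs.** Five sessions a week in weeks 1–3 and three a week from week 4, capped at 10 weeks (Dosing schedule); tier cut-points of 15, 21 and 36 (Exposure tiers); assessment 0–7 days before surgery (Table 1).

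**Step 1: reproduce the plan's figures.** Planned sessions by the end of week w, for w from 3 to 10, are S(w) = 15 + 3(w − 3).
- S(3) = 15, S(5) = 15 + 6 = 21, S(10) = 15 + 21 = 36.
- These match the three tier definitions. Also S(4) = 18.

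**Step 2: sessions after the outcome, worst case.** Assume full adherence and assessment exactly 7 days before surgery. The count at assessment is then S(w − 1).

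| Surgery at end of week | Counted to surgery | Counted to assessment | After the outcome | Tier as analysed | Tier at assessment |
|---|---|---|---|---|---|
| 4 | 18 | 15 | 3/18 = 17% | A | A |
| 5 | 21 | 18 | 3/21 = 14% | B | A |
| 6 | 24 | 21 | 3/24 = 12.5% | B | B |
| 10 | 36 | 33 | 3/36 = 8% | C | B |

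Among surgeries at the end of weeks 4 to 10, the tier changes only at weeks 5 and 10.

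**Step 3: a less extreme picture.** The article gives no distribution of surgery dates, so this step rests on assumptions: surgery uniform over weeks 4–10 or 4–14, assessment uniform over the 7 days before surgery, adherence 85% or 100%. A simulation under these settings gives:
- a mean of 0.8 to 1.5 sessions after the outcome;
- 7% to 14% of participants in a different tier (0.07 × 20 = 1.4 to 0.14 × 20 = 2.8, so about 1 to 3 of the planned 20);
- a correlation of 0.98 to 0.99 between the count to surgery and the count to assessment.

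The tier analysis is moderately affected and the continuous analysis hardly at all.

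**Step 4: the gap after week 10.** Days from the end of week 10 to assessment = 7 × (surgery week − 10), less 0 to 7 days.
- Week 12: 14 less 0–7 = 7–14 days.
- Week 14: 28 less 0–7 = 21–28 days.
- Week 16: 42 less 0–7 = 35–42 days.

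The count stays at 36 or below throughout. Weeks 12, 14 and 16 are illustrations; the article does not say how many participants will wait that long.

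**The case against.** The strongest reply is that this is a narrow matter in hypothesis-generating analyses of about 20 people, and that a cut-off date for a session count is a detail for an analysis plan. Several parts of that reply stand.

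- Counting to surgery is right for the feasibility proportions and for every postoperative outcome.
- The step 2 figures are worst cases.
- The mixed model described for MADRS-S lists time and baseline severity as fixed effects and no exposure term, so for MADRS-S the exposure analysis rests on the stated hypothesis.
- No cut-off is stated for the continuous count; that it also runs to surgery is inferred from the tier definition.
- Mood just before surgery is a legitimate target even after an untreated gap, and any week-10 MADRS-S value would enter the mixed model.

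The reply does not remove the point. The article itself fixes the tier by sessions before surgery and uses that tier as an exposure variable for outcomes measured earlier.

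A reader might infer three stronger things that the documents do not support:

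- **That only participants operated on after week 10 can reach the longest exposure, so Tier C is always measured off treatment.** Surgery at the end of week 10 also allows 36 sessions, with assessment within the preceding week.
- **That the plan treats later sessions as a cause of the earlier outcome.** It speaks of associations, and the Discussion puts transparency and interpretability ahead of causal inference. The time order is still wrong for an association.
- **That the week-10 value could simply replace the preoperative one at no cost.** Table 1 schedules none for ODI or PROMIS Physical Function, Pain Interference is optional, and the swap would change the principal exploratory outcome.

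**Conclusion.** The point holds for the exploratory exposure-response analyses of preoperative outcomes, and only there. As written, the tier can include up to about 3 maintenance sessions given after the outcome: at most 17%, 14% and 8% of counted sessions for surgery at the end of weeks 4, 5 and 10, assuming full adherence and a 7-day interval. Participants near a cut-point can be placed one tier too high. Under the assumed timing distributions that is about 1 to 3 of 20, which matters when tiers are small. The continuous analysis is little affected.

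The gap after week 10 is a separate issue. It affects only participants operated on later than that, and its size depends on surgical delays for which the article states no maximum; the planned end of follow-up in 2027 is only a practical bound. Those operated on at about week 10 are not affected by it.

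The primary feasibility and acceptability results are untouched.

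**What to change.** 1. Keep sessions completed before surgery as the exposure for the feasibility tiers and for postoperative outcomes.
2. For every exposure-response analysis of a preoperative outcome, define exposure (count and tier) as complete sessions up to the date of that assessment.
3. Keep the preoperative assessment as the endpoint of the principal exploratory outcome, and report the days from last session to assessment for each participant.
4. For participants operated on after week 10, add a sensitivity analysis using the week-10 value where Table 1 schedules one: MADRS-S, the two pain ratings, and Pain Interference if collected. Do not extend it to ODI or PROMIS Physical Function. Reconcile the outcome text, which lists weeks 0, 1, 4, 7 and a preoperative visit for MADRS-S, with the Table 1 footnote, which adds week 10.

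Items 1 to 3 cost a few sentences of analysis wording, because the usage logs described under Onboarding and monitoring already record session date and completion status. Item 4 uses only measurements that Table 1 already lists, once the week-10 MADRS-S visit is confirmed. No treatment schedule changes. The rules should be fixed before outcomes are seen, so that the exposure window is not chosen afterwards.
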